## Abstract

**Background:**

Stress-related disorders are a growing public health concern. While stress is a natural and adaptive process, chronic exposure to stressors can lead to dysregulation and take a cumulative toll on physical and mental well-being. One approach to coping with stress and building resilience is through Mindfulness-Based Stress Reduction (MBSR). By understanding the neural mechanisms of MBSR, we can gain insight into how it reduces stress and what drives individual differences in treatment outcomes. This study aims to establish the clinical effects of MBSR on stress regulation in a population that is susceptible to develop stress-related disorders (i.e., university students with mild to high self-reported stress), to assess the role of large-scale brain networks in stress regulation changes induced by MBSR, and to identify who may benefit most from MBSR.

**Methods:**

This study is a longitudinal two-arm randomised, wait-list controlled trial to investigate the effects of MBSR on a preselected, Dutch university student population with elevated stress levels. Clinical symptoms are measured at baseline, post-treatment, and three months after training. Our primary clinical symptom is perceived stress, with additional measures of depressive and anxiety symptoms, alcohol use, stress resilience, positive mental health, and stress reactivity in daily life. We investigate the effects of MBSR on stress regulation in terms of behaviour, self-report measures, physiology, and brain activity. Repetitive negative thinking, cognitive reactivity, emotional allowance, mindfulness skills, and self-compassion will be tested as potential mediating factors for the clinical effects of MBSR. Childhood trauma, personality traits and baseline brain activity patterns will be tested as potential moderators of the clinical outcomes.

**Discussion:**

This study aims to provide valuable insights into the effectiveness of MBSR in reducing stress-related symptoms in a susceptible student population and crucially, to investigate its effects on stress regulation, and to identify who may benefit most from the intervention.

**Trial registration:**

Registered on September 15, 2022, at clinicaltrials.gov, NCT05541263.

## Background

Stress-related mental disorders, such as anxiety, depression, and post-traumatic stress disorder are a significant public health concern with substantial and often debilitating mental and physical symptoms [1]. In 2017, 540 million people were affected world-wide by anxiety and depression alone [2]. These disorders contribute to shorter life expectancy [3], lower quality of life [4], as well as a large economic burden to society [5]. As the term “stress-related disorders” suggests, a common component in the development of such disorders is (chronic) exposure to stressors. These can be internal or external factors creating a (perceived) threat to one’s well-being. Exposure to stressors can prompt a response (i.e. the stress response) that includes a complex set of psychological, cognitive, neural, metabolic, immunological, and physiological changes developed to aid individuals to better adapt to challenges in their life [6]. However, chronic exposure to stressors can lead to a dysregulation of these complex interactions causing a cumulative toll on physical and mental well-being, described as allostatic overload [6, 7].

Perceived stress is a robust predictor of the development of psychopathology, and stress-regulation processes have been shown to play a protective role in that respect [8]. Therefore, adequate coping with stress may substantially contribute to stressnresilience, preventing the deterioration of mental health. An effective approach with this very aim is Mindfulness Based Stress Reduction (MBSR) [9]. Introduced into clinical practice in 1979 by Kabat-Zinn, mindfulness is defined as non-judgemental present-moment, intentional awareness. Mindfulness training thus promotes deliberately paying attention with a curious, open attitude to one’s habitual affective, cognitive, and behavioural reactions to stress, ultimately learning to deal more effectively with stressful situations [10, 11]. This intervention has been shown to be effective in reducing symptoms of perceived stress, anxiety, and depression in healthy and clinical populations [9, 12]. However, these interventions are not universally effective, and there is a growing recognition for the need to understand individual differences in treatment response.

A mechanistic understanding of stress regulation via mindfulness could shed light on *how* MBSR reduces stress and *what* drives individual differences in treatment outcome. Research into psychological mechanisms of MBSR and derivatives of this program, described as Mindfulness-Based Interventions (MBIs), has shown that self-reported mindfulness skills and decentring play a mediating role in stress and anxiety symptom reduction [13, 14]. Other potential mechanisms include different emotion regulation processes, reducing ruminative thoughts, and acceptance, suggesting that mindfulness can influence affective processing [15]. These mechanisms provide a framework for stress regulation that might be considered different to other common stress management strategies, such as cognitive reappraisal, which depend mainly on enhancing executive control [16]. Additionally, there is some evidence that MBIs can influence different cognitive processes [15, 17]. Various attention-related and working memory-related functions have been shown to be affected following a MBI, although evidence is limited [18, 19].

In line with psychological research, research on the neural mechanisms of MBIs provides preliminary evidence on the involvement of neural structures engaged in both cognitive and affective processing [20]. Some of the most robust findings have included structural and functional changes in brain regions such as the insula, the amygdala, the anterior cingulate cortex (ACC), and multiple prefrontal cortex (PFC) regions (e.g., dorsolateral PFC and ventromedial PFC) [20, 21]. Interestingly, these regions are considered core nodes of three large-scale brain networks, which are thought to play a role in the stress response as well as in the development of various stress-related disorders [22–24]. First, the salience network (SN) is considered to be central in affective processes integrating relevant autonomic, interoceptive and emotional information [25]. Second, the executive control network (ECN) is involved in higher-order cognitive functions, such as goal-directed problem solving, top-down control, and decision making [26]. Third, the default mode network (DMN) is associated with self-referential and social-cognitive processing [27]. In addition, a recent review of accumulating data suggests that mindfulness is specifically related to functional connectivity changes in these networks [28]. Therefore, the clinical effects of MBSR could potentially be driven by a change in these networks’ configurations under stress, constituting a more adaptive stress-regulation.

In the current study we focus on how MBSR can affect different aspects of stress regulation in terms of behaviour, self-report measures, physiology and brain activity, across two orthogonal dimensions. The first dimension covers stress-regulation processes spanning from regulation directly related to external stressors (exogenously driven regulation) to regulation related to internal stressors, such as ruminative thoughts, or stressed states not directly related to external stressors, e.g., in the aftermath of acute stress (endogenously driven regulation). The second dimension spans from stress-related processes requiring active, goal-directed responses (i.e., explicit regulation) to stress-related processes when no action is required (i.e., implicit regulation). This framework yields four domains of stress-regulation processes. For example, exogenous-explicit regulation occurs while trying to deliberately apply emotional regulation during a stressful event such as an exam. Exogenous-implicit regulation describes processes like automatic reactions to fearful stimuli such as the anticipation of a sharp pain. Endogenous-explicit regulation involves processes like deliberate reappraisal of intrusive thoughts. An example of endogenous-implicit regulation is one’s automatic reactions to anxious internal states (e.g., rumination).

We apply this framework in the design of the current longitudinal randomised controlled trial, whereby we investigate the effects of MBSR on a preselected, Dutch, university-student population with high self-reported levels of perceived stress. University students have been shown to be a population at risk of developing stress-related symptoms. Frequent examination periods, assignment deadlines, restricted financial support, time pressure to complete studies, and future uncertainty are some of the main sources of prolonged stress for students [29]. This may have implications for academic performance, private life, and overall health, thus leading to increased personal and societal burden. There is already evidence for a beneficial effect of MBSR on stress in general student samples [9]. However, studies targeting specifically highly stressed students, those presumably most at risk for mental health problems, are lacking. This is a population that may greatly benefit from enhanced stress-regulation potentially preventing stress-related symptomatology. It is therefore key to establish whether MBSR is indeed effective in reducing stress in this specific student population.

Thus, the goals of the current study are to (1) establish clinical effects of MBSR in a population of Dutch university students with high levels of perceived stress, (2) identify the effect of MBSR on stress regulation, (3) assess the role of large-scale networks in this process, and (4) identify for whom MBSR might be more beneficial. Our main hypothesis regarding aim (1) is that MBSR is effective at reducing self-reported perceived stress in a population of highly stressed university students, sustained over a 3-month follow-up period. We expect to replicate previous studies showing the efficacy of MBSR within student populations [30–33] and we expect that MBSR is also effective at reducing other relevant clinical symptoms in this population, such as depression and anxiety symptoms [9]. Regarding aims (2) and (3) (i.e., the effects of MBSR on stress regulation and the role of large-scale networks in this process), we hypothesise that MBSR leads specifically to concurrent enhancement of cognitive control *and* affective processing across the different domains of stress-regulation described above. Moreover, we expect that these measures at baseline will be important in predicting individual differences in effectiveness of MBSR, and that changes in these measures will be accompanied by changes at the clinical level for aim (4).

## Methods

### Design

This study is a two-arm randomised, wait-list controlled trial with ethical approval from the local medical-ethical committee (METC Oost-Nederland), see Fig. 1. Participants are randomised into a treatment and a wait-list control group after baseline measurements including clinical, neurocognitive, and ecological momentary assessments. In the following two months, the treatment group participates in an MBSR training, and the wait-list group receives no planned intervention for two months, serving the purpose of assessing the effect of the intervention on the study outcomes against not receiving treatment during the same time-period. Post-treatment measurements take place three months after baseline, and they include another set of clinical, neurocognitive, and ecological momentary assessments. Six months after baseline there is a follow-up clinical assessment. After this assessment, the participants in the wait-list group receive the MBSR training, after which they complete a final clinical assessment.

**Fig. 1 Fig1:**
[figure not shown]
Study design. CA: clinical assessments, NA: Neurocognitive assessments, EMA: Ecological Momentary Assessments

### Population

We aim at recruiting 60 students per group (total: 120) from Radboud University, Radboudumc, and university of applied sciences Hogeschool Arnhem Nijmegen, with high perceived stress (see sample size calculation in analysis section). This target includes an expected attrition rate of 10%, leading to a total sample of 108 participants. We include students who are above 18 years, able to give consent, and who are mildly to highly stressed achieving a score ≥ 16 on the perceived stress scale (PSS) [34, 35]. Participants are excluded (1) if they are receiving current specialised psychological or psychiatric treatment or medication, (2) if they have insufficient comprehension of the Dutch language, (3) if they have physical, cognitive, or intellectual impairments interfering with participation, such as deafness, blindness, or sensorimotor handicaps, (4) if they were formerly or currently involved in a Mindfulness Based Stress Reduction or a Mindfulness Based Cognitive Therapy training, (5) if they have a current drug or alcohol addiction, and (6) if they have contraindications for MRI scanning (e.g., pacemaker, implanted metal parts, deep brain stimulation, claustrophobia, epilepsy, brain surgery, pregnancy).

### Intervention

The mindfulness intervention used in this study is an MBSR training based on the MBSR programme developed by Kabat-Zinn (1982) and has been widely investigated in the last few decades [9, 36]. The training consists of 8 weekly group sessions lasting 2,5 h. A silent day of 6 h is also included, as well as daily home practice assignments of a recommended 45 min. During the training participants learn to intentionally focus their attention on the present moment in an accepting and non-judgemental way, rather than ruminating about past and future experiences. The training includes formal exercises during which participants will practice the body scan, sitting meditation, walking meditation and mindful movement. Informal exercises are also included, such as performing a daily activity with full attention to the present experience. The training is led by qualified teachers meeting the advanced criteria of the Association of Mindfulness Based Teachers in the Netherlands and Flanders (www.vmbn.nl).

### Randomisation

Groups of maximally 20 participants at a time (because of limitations in scanning capacity) are recruited and are randomly assigned to either the MBSR or waitlist control condition. This ensures that equal numbers of experimental and control group participants are recruited at any given time-period. Randomisation is conducted after baseline clinical, neurocognitive, and ecological momentary assessments. The procedure is carried out by an automated custom Python script using computer-generated random numbers, taking into account stratification for gender and University (i.e., Radboud University, or Hogeschool Arnhem Nijmegen). Baseline measurements occur before group assignments and therefore both participants and researchers are blinded to these measurements. Post-treatment measurements are not blinded.

### Questionnaires (clinical assessments)

We measure perceived stress with the Perceived Stress Scale (PSS), a 10-item questionnaire (range 0–40), which evaluates the degree to which an individual perceives their life as unpredictable, uncontrollable, and overloading. This scale was found to have good internal consistency (*α* = 0.84–0.86) and test–retest reliability (*r*_*tt*_ = 0.85) [34, 35].

Depressive symptoms are assessed with the Inventory of Depressive Symptomatology Self-Report (IDS-SR), which is a 30-item self-report measure of depressive symptom severity (range 0–84). This scale was found to have excellent internal consistency (*α* = 0.93) [37, 38].

Anxiety symptoms are assessed with the State and Trait Anxiety Inventory (STAI), which is a self-reported 20-item measure of trait (range 20–80) and a self-reported 20-item measure (range 20–80) state anxiety. The questionnaire was found to have good internal consistency for state (*α* = 0.83–0.92) and trait (*α* = 0.86–0.92). Test–retest reliability was good for trait (*r*_*tt*_ = 0.73–0.86) and poor for state (*r*_*tt*_ = 0.16–0.62) [39, 40].

Alcohol use is assessed with the Alcohol Use Disorders Identification Test (AUDIT), which is a 10-item screening tool developed by the World Health Organization (WHO) to assess alcohol consumption, drinking behaviours, and alcohol-related problems (range 0–40). The questionnaire was found to have high internal consistency (*α* = 0.80–0.86) and high test–retest reliability (*r*_*tt*_ = 0.84) [41–43].

Childhood trauma is assessed with the Maltreatment and Abuse Chronology of Exposure Scale (MACE-X), which is a self-reported questionnaire which is used to assess the extent as well as the severity of traumatic experiences of participants in their childhood. We use a Dutch translation of the original English questionnaire. The original questionnaire in English was found to have high test–retest reliability (*r*_*tt*_ = 0.91) [44].

Personality traits are assessed with the NEO Five Factor Inventory (NEO-FFI), which is a 60-item self-reported questionnaire and covers a set of five broad personality trait dimensions or domains: Extraversion, Agreeableness, Conscientiousness, Neuroticism, and Openness to Experience. The questionnaire was found to have high internal consistency for all subscales (*α* = 0.74–0.89) and test–retest reliability (*r*_*tt*_ = 0.86–0.90) [45].

Repetitive negative thinking is assessed with the Perseverative Thinking Questionnaire (PTQ), which is a 15-item self-reported questionnaire and is used to assess repetitive negative thinking in a content-free manner (range 0–60). The questionnaire was found to have excellent internal consistency (*α* = 0.94–0.95) and satisfactory test–retest reliability (*r*_*tt*_ = 0.69) [46].

Cognitive reactivity is assessed with the Leiden Index of Depression Sensitivity – Revised (LEIDS-R), which is a 34-item self-report questionnaire measuring cognitive reactivity to sadness (range 0–136). The questionnaire was found to have good internal consistency on all subscales (*α* = 0.77–0.89) [47].

The concept of allowing of emotions is assessed with the Acceptance and Action Questionnaire (AAQ), which is a 10-item self-reported questionnaire measuring psychological flexibility and experiential acceptance (range 10–70). The questionnaire was found to have good internal consistency (*α* = 0.84) and test–retest reliability (*r*_*tt*_ = 0.79–0.81) [48].

Mindfulness skills are assessed with the short version of the Five-Facet Mindfulness Questionnaire (FFMQ-SF), which is a 24-item self-reported questionnaire measuring five aspects of mindfulness, namely observation, description, aware actions, non-judgemental inner experience, and non-reactivity. The questionnaire was found to have good internal consistency for all subscales (*α* = 0.73–0.91) [49].

Self-compassion is assessed with the short version of the Self-Compassion Scale (SCS-S), which is a 12-item self-report questionnaire consisting of six components, including self-kindness, self-judgment, common humanity, isolation, mindfulness, and over-identification. The questionnaire was found to have good internal consistency (*α* = 0.86) [50].

Self-reported stress resilience is assessed with the Connor-Davidson Resilience Scale (CD-RISC), which is a 25-item questionnaire (range 0–100). The questionnaire was found to have good internal consistency (*α* = 0.89) and test–retest reliability (*r*_*tt*_ = 0.87) [51].

Positive mental health is assessed with the short form of the Mental Health Continuum (MHC-SF), which is a 14-item self-report questionnaire that assesses emotional, psychological and social well-being (range 0–70). The questionnaire was found to have good internal consistency (*α* = 0.89) and moderate test–retest reliability (*r*_*tt*_ = 0.65–0.70) [52].

All self-report questionnaire data are acquired using CastorEDC, an Electronic Data Capture program (https://www.castoredc.com/) during measurement visits.

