#### Implicit, exogenous stress-regulation – fear conditioning and extinction task

Implicit, exogenous stress regulation is assessed using a differential fear conditioning and extinction paradigm in the MRI scanner, since this task involves measuring spontaneous responses to an external stressor. Mild electrical stimulation to the fingers is used as the unconditioned stimulus (US). Two shapes are used as conditioned stimuli (CS), and they are presented for 4 s on top of a specific background image (the same for both stimuli) with an average intertrial interval of 12 s. One of the two shapes is sometimes paired with a US during the final 200 ms of the stimulus presentation (CS +) and the other one is never paired with the US (CS-). Reinforcement rate using the US is set at 35%. After fear conditioning has occurred, we proceed with a fear extinction task inside the MRI scanner. The two CS are presented as described in the previous paragraph, however the CS + is not paired with the US anymore. Furthermore, the background image is changed, representing a different context during extinction learning. On the following day, an extinction recall task is performed outside of the scanner, in order to assess the strength of the extinguished memory. The background image is the same as during fear extinction and the CS + and CS- are presented without the administration of electrical stimulations (i.e., the US). A fear renewal task follows, to assess the strength of the fear memory in the context it was acquired in. The background image is therefore the same as the one used during the fear conditioning task. The CS + and CS- are presented as described in the fear conditioning task, however without administration of electrical stimulations.

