#### Baseline measurements

After inclusion, the participant’s baseline measurements are acquired. First, two visits (on consecutive days) at the Donders Centre for Cognitive Neuroimaging (DCCN) are scheduled. On the first visit participants are asked to perform some of the neurocognitive assessments (Fear Conditioning task, Emotional Conflict Resolution task, and Resting State fMRI task). On the second visit participants are asked to perform a short task, part of the Fear Conditioning task. In addition, they undergo clinical assessments in the form of questionnaires on both days. Participants will then follow a week of ecological momentary assessments, during which they are asked to answer multiple short questionnaires during their daily life. After these baseline measurements, participants are randomly assigned to two groups as described earlier.

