#### Post-intervention

As soon as the MBSR training has concluded, all participants are asked to visit the DCCN for their post-treatment measurements. These visits (visit 3 & 4) are scheduled on consecutive days and will involve the same neurocognitive and clinical assessments as the baseline measurements, with the addition of the Real-time fMRI Neurofeedback task. In addition, another ecological momentary assessment week is planned.

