#### Clinical symptoms

We expect that participants who follow the MBSR training will show a larger decrease in perceived stress, anxiety, and depressive symptoms compared to wait-list control participants. To statistically test the difference in perceived stress between the MBSR and the wait-list control groups post-treatment we will use an ANCOVA, including baseline PSS scores as covariates. Thus, the dependent variable will be post-treatment PSS score and group will be used as a between subject factor with two levels (MBSR, wait-list). The primary analysis will be performed with an intention-to-treat approach and sensitivity analyses will be conducted with different scenarios of imputed datasets to examine the influence of missing data on outcomes. Additional covariates will be added to account for individual differences (university, sex, age, and recruitment wave). Similar analyses will be performed on the following secondary clinical measures: depressive and anxiety symptoms, alcohol use, stress resilience, positive mental health and daily-life stress. Perceived stress at follow-up will be assessed by a linear mixed effect regression analysis with group (MBSR, wait-list), time (baseline, post-treatment), university, sex, age, and recruitment wave as fixed factors, as well as a group x time interaction. The intercept will be allowed to vary across participants to account for between-subject variability. Other clinical assessments, such as those assessing repetitive negative thinking, cognitive reactivity, allowing of emotions, mindfulness skills, self-compassion will be tested as potential mediating factors to determine whether changes in those scores after treatment can explain changes in the primary outcome at follow-up (i.e., PSS score). Mediation analyses will be conducted on the per-protocol sample (i.e., those participants who attended 50% or more of the training). Clinical assessments such as those assessing childhood trauma and personality traits at baseline will be tested as potential moderators of the clinical outcome.

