### Update

We are currently in the process of recruiting and testing participants since April 2021. It is expected that reaching the total sample size which was reported on trialregister.gov will be a challenge. One of the main factors contributing to this is the impact of the COVID-19 pandemic lockdowns, since during the first year of recruitment students were largely studying remotely. In order to address this issue, the study’s recruitment period has been extended by a year, and recruitment efforts have been reassessed. However, there is reason to believe that our sample size estimate is very conservative. The meta-analysis by Khoury et al. (2015) suggests that the combined effect size from studies investigating MBSR on student populations is higher than our original estimate. They report even higher combined effect size on stress measures in studies with various healthy populations, including students. This suggests that our trial is better powered than initially thought. In addition, effect sizes reported in studies investigating the effects of MBSR on stress regulation tasks, similar to the ones we deploy, suggest that the current trial will be well powered to detect these effects [57–60]. This makes us confident that we will be able to detect differences in perceived stress and our stress regulation tasks despite potentially reaching a smaller sample size.

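### As written, the primary PSS score can be given only at on-site visits, so a participant who attends neither post-treatment visit has no observed primary outcome, although the form is short and electronic

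*Protocol article*

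**What the plan says.** Under Questionnaires (clinical assessments), the Protocol article sets one collection rule for all self-report instruments, the PSS included: "All self-report questionnaire data are acquired using CastorEDC, an Electronic Data Capture program (https://www.castoredc.com/) during measurement visits".

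Under Post-intervention, "all participants are asked to visit the DCCN for their post-treatment measurements". On their content: "These visits (visit 3 & 4) are scheduled on consecutive days and will involve the same neurocognitive and clinical assessments as the baseline measurements", with the neurofeedback task added. Under Baseline measurements, the scanner tasks belong to the first visit and only a short part of the fear conditioning task to the second. On the questionnaires: "In addition, they undergo clinical assessments in the form of questionnaires on both days".

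Under Clinical symptoms, the dependent variable is the PSS score after treatment, and "The primary analysis will be performed with an intention-to-treat approach". Imputed datasets are mentioned only for sensitivity analyses. The retention measure described under Recruitment is e-mail reminders. The sample size section allows for 10% attrition.

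Two other sections show that the trial already collects self-report remotely. The screening survey, which includes the PSS, is completed online (Recruitment), and the daily-life surveys are completed on a smartphone app (Ecological Momentary Assessments).

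**The concern.** An intention-to-treat comparison needs outcomes from everyone randomised, especially from those who stopped the training. They may have the least reason to come back to the laboratory. The collection rule makes the primary outcome depend on attendance, and the first post-treatment day is demanding: fear conditioning with electrical stimulation, the socially evaluated cold pressor with mental arithmetic, and scanning. Someone who cannot or will not travel to either visit has, on the text, no way to give a PSS score. Reminders do not solve that.

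Some missing primary outcomes are therefore avoidable. If non-attendance is related to stress or to disengagement from training, the missing scores are not a random subset, and imputation scenarios can only explore the consequence, not recover the values.

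**Working it through.** **1. What follows from the text**

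- Every questionnaire is acquired during a measurement visit (Questionnaires section).
- The post-treatment visits are 3 and 4, at the imaging centre (Post-intervention).
- No other route is described. A participant who attends neither visit therefore has no observed post-treatment PSS.
- The two days differ. The baseline schedule puts scanning, stimulation and the cold pressor on the first day. For the second day of the fear task, "On the following day, an extinction recall task is performed outside of the scanner", and for that recall task "The background image is the same as during fear extinction and the CS + and CS- are presented without the administration of electrical stimulations". Questionnaires are given on both days. The article does not say on which day the PSS is given.

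**2. The plan's own sample size**

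Inputs (Sample size calculation): d = 0.4, r = 0.7, α = 0.05, power 80%. Sidedness is not stated; two-sided is assumed.

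- Per group, unadjusted: an exact two-sample t-test needs 99.08.
- Multiplied by (1 − r²) = 1 − 0.49 = 0.51: 99.08 × 0.51 = 50.5, so 51 per group.
- The article states 54. The stated inputs do not reproduce it; the gap of 3 is on the conservative side and does not bear on this point.
- Attrition: 54 / (1 − 0.10) = 60, as stated.

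**3. Power by share of post-treatment PSS scores lost**

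Effective d = 0.4 / √0.51 = 0.560, two-sided α = 0.05, exact t-test, 60 recruited per group, equal loss in both arms. Only the 10% comes from the article; the other rates are assumptions.

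| Loss | Analysed per group | Power |
|---|---|---|
| 0% | 60 | 86.1% |
| 5% | 57 | 84.2% |
| 10% | 54 | 82.2% |
| 15% | 51 | 80.0% |
| 20% | 48 | 77.5% |
| 25% | 45 | 74.8% |

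Recovering half of a 10% loss (54 to 57 per group) adds 84.2 − 82.2 = 2.0 points. Recovering all of it adds 86.1 − 82.2 = 3.9 points. Recovering half of a 20% loss (48 to 54) adds 82.2 − 77.5 = 4.7 points.

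**4. Possible bias**

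If a share *l* of one arm is missing, and those participants differ from the observed ones by *k* SD, the observed mean of that arm is off by *l* × *k*. Both ranges below are assumptions.

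- *l* = 10%, *k* = 0.25: 0.10 × 0.25 = 0.025 SD
- *l* = 20%, *k* = 0.5: 0.20 × 0.5 = 0.10 SD
- *l* = 30%, *k* = 1: 0.30 × 1 = 0.30 SD

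The planned effect is 0.4 SD. The lower end is negligible and the upper end is not. Baseline adjustment would remove the part of *k* that baseline PSS explains. The article gives nothing that fixes *l* by arm, *k*, or the sign.

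**The case against.** The best defence is that the article states a routine collection procedure, not a prohibition, and that rules for missed or partial visits usually sit in a full protocol, which is not shown. Attrition is also anticipated: there are reminders, a 10% allowance and imputation scenarios. Completion at a visit gives a uniform setting for a self-reported primary outcome, which has value. Finally, people who ignore reminders may also ignore an e-mailed form.

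Much of this stands, and it rules out several stronger readings that a reader might infer:

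- *That both post-treatment days are scanner days with stimulation and a cold pressor.* Only the first is. The second-day task is outside the scanner and without stimulation, and questionnaires are given that day too. Visit 5 consists of clinical assessments only, so the burden argument does not extend to follow-up.
- *That anyone who declines the tasks or the scan loses the outcome.* Nothing in the article says so. Such a person can still attend and fill in the form.
- *That loss will differ between arms in a known direction.* The wait-list group still awaits its training at that point, but the article does not make that training conditional on visits 3 and 4. The direction is open.
- *That the Update section shows a problem with outcome loss.* The remark "It is expected that reaching the total sample size which was reported on trialregister.gov will be a challenge" concerns recruitment. It matters here only because fewer recruits leave less room for missing outcomes.

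What the defence does not remove is the gap for those who attend neither visit. The article does not merely omit a fallback; it says that all questionnaire data come from visits. If the full protocol has a remote route, that sentence needs correcting.

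**Conclusion.** The point holds in limited form. It is a design weakness, not a contradiction or a wrong figure. As written, non-attendance at both post-treatment visits means no observed primary outcome, in a trial that already collects the same scale online at screening.

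Power is a secondary matter. It stays at or above 80% up to about 15% loss, given 60 recruited per group, d = 0.4, r = 0.7 and a two-sided α of 0.05. Any mix of recruitment shortfall and missing scores that leaves fewer than 51 analysed per group falls below 80%.

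The main reason to act is possible bias in the intention-to-treat comparison. Its direction and size cannot be determined from the article; the illustrative range of 0.025 to 0.30 SD rests wholly on assumed inputs. Because the remedy is cheap, the change is worth making.

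**What to change.** Amend the collection rule in the Questionnaires section along these lines: *Participants complete the questionnaires at the visit. Any randomised participant who does not attend the post-treatment or follow-up visit, including anyone who stopped training, is sent the same CastorEDC questionnaires to complete remotely in the same time window.*

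Record the completion mode (on-site or remote) for each assessment, and add a sensitivity analysis of the primary ANCOVA restricted to on-site completions.

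The cost is a minor amendment, one additional CastorEDC invitation and a mode variable, with no extra visits or staff. The downside is that a few participants answer in a different setting; the mode variable and the sensitivity analysis show whether that matters. The change will not recover everyone, and it does nothing for recruitment. The article reports recruitment and testing as still under way, so at that stage the change could still apply to later participants.
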